## Methods/design

### Study design

The randomized controlled trial will follow the recommendations of the CONSORT (Consolidated Standards of Reporting Trials) group, which is considered a gold standard in clinical practice regarding devising interventions as well as their reporting [43]. The study design is depicted in Fig. 1. The study will take place between October 2020 and February 2021. In order to reach the target sample size, the second round of data collection will take place between January 2021 and May 2021, and additional rounds of data collection will be carried out if needed. Data collection in both intervention groups (i.e., CBT- and MBSR protocol) and the control group will be carried out immediately before (T1) and after the intervention (T2). During the 6-week intervention period, weekly questionnaires will be sent out to participants. The follow-up data collection will take place 3 months after the end of the intervention (T3). During T1, T2 and T3, participants will be asked to fill out questionnaires addressing all studied constructs, whereas the weekly questionnaire will only encompass the central mechanisms and primary study outcomes (i.e., work-related maladaptive thinking patterns, mindfulness, psychological detachment, and burnout). During the intervention period, participants from both intervention groups will receive e-mail notifications every Monday and Thursday with information about the assignments and exercises. The initial e-mail will include instructions on how to access the online platform with CBT and MBSR exercises. The notification every Monday will remind participants to fill out the weekly questionnaire before they start with the new exercise. All exercises from previous weeks will be visible on the online platform. Upcoming exercises will not yet be available to ensure that participants will not skip the activities or perform them in random order. The online platform will automatically monitor whether the participants followed the instructions and performed the respective exercises. In case of non-compliance, reminders will be sent out the following day. After the intervention, participants from the waitlist control groups will receive access to the online platform and all intervention materials, which they can perform in any order. They will receive weekly e-mails reminding them to perform the exercises and encouraging them to practice them. After the intervention, each participant will have the opportunity to request individualized feedback on his or her results.

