### Participants and recruitment

The participants will be recruited from various organizations in Slovenia partnered with the leading institution and through different media channels. The intervention will also be advertised through university newsletters and webpages as well as a well-known Slovenian mental health platform. Interested participants will be able to apply for the study via an online form. Although we will not specifically exclude any professions, employees with knowledge-intensive jobs and high-stress occupations will be primarily targeted [44]. The recruitment stage will begin in August 2020. Following previous intervention studies in the workplace context (e.g., [17, 18]), participants will be pre-screened for eligibility. They will have to meet the following inclusion criteria: 1) being aged 18 or above, 2) working a minimum of 40 h per week and currently not on sick leave, 3) ability to commit (at least) 2 h per week to the online training, 4) ongoing internet connection and computer accessibility, 5) reporting difficulties with psychological detachment from work and burnout at least to a moderate extent. Participants undergoing other forms of treatment (psychotherapy, pharmacotherapy) or who have a clinical diagnosis of mental illness will not be eligible to participate. They will, however, receive additional information on relevant health care services and a link to mindfulness and CBT exercises they can practice on their own. Those eligible to participate will receive detailed information about the intervention and an online informed consent form. Participants who will commit to the study will be randomly assigned to one of the three groups. Following the approach by Querstret and colleagues [17], block randomization based on gender will be used. Participants will be randomized within blocks in such a way that an equal number of females and males are assigned to each of the groups because women exhibit more rumination and difficulties detaching from work at home (e.g., [17]). In order to control for expectations about potential benefits of the interventions, participants will be blinded to the intervention. Both the CBT-based and the MBSR intervention will be advertised as occupational stress-reduction interventions. The participants assigned to the waitlist control group will only be asked to participate in the study and fill out the questionnaires. They will also receive information regarding the delayed starting date of the training.

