### Measures

All four questionnaire batteries (pre-screening, T1, T2, T3) will include measures of burnout and psychological detachment (primary outcomes). In the pre-screening questionnaire, these two constructs will be accompanied by additional questions aimed at collecting data on background variables (e.g., demographic data). The questionnaire battery, which will be administered at T1, T2, and T3, will also include the following constructs: quality of sleep, work engagement, workaholism, work-family conflict, positive and negative affect, life satisfaction, depression, anxiety, stress (secondary outcomes), mindfulness, work-related maladaptive thinking patterns (potential mechanisms of change), supervisor support for recovery, segmentation supplies, unfinished tasks and time pressure (potential moderators). Furthermore, some additional background variables related to the evaluation of the intervention will be asked at T2 (directly after the intervention, e.g., overall satisfaction with the intervention).

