### Statistical analysis

#### Sample size calculation

The G*Power 3.1 software was used to determine the minimum number of participants that need to be recruited [64]. We set the expected effect size to medium (*f(V)* = .25), the probability of a Type I error to α = .05, the statistical power (1-β) to .95 and chose a two-way repeated measures MANOVA (multivariate analysis of variance) with time (3 levels: pre, post, and follow-up) as the within-subjects factor and group (3 levels: CBT, MBSR, and control) as the between-subjects factor as the main statistical test. Given these specifications, the required total sample size is 151 participants (approximately 50 participants per group). In case of non-adherence and/or drop-out, the total sample size of 98 participants (approximately 33 participants per group) suffice with a more standard power level of .80.

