#### Effect evaluation

The analyses will be carried out with SPSS [88] and Mplus [89]. The significance level used in the analyses will be .05. The main research questions (i.e., group differences in psychological detachment from work and burnout) will be analyzed with two separate two-way repeated measures analyses of variance (ANOVAs), with time as the within-subjects factor (3 levels: pre, post, follow-up) and group as the between-subjects factor (3 levels: CBT, MBSR, control), for each of the main outcomes separately. Significant interactions will be followed up with a simple effects’ analysis, using the Bonferroni correction to adjust for multiple testing.

The effects of the intervention on the secondary outcomes (i.e., general and work-related well-being) will be analyzed with a two-way repeated-measures MANOVA, with time as the within-subjects factor and group as the between-subjects factor. This analysis is contingent upon moderate correlations between the dependent variables [90]. Therefore, we will first examine correlations between the secondary outcome variables. Significant interaction effects will be followed-up with ANOVAs for each of the dependent variables and a discriminant descriptive analysis to further examine the effects. The moderation (i.e., supervisor support for recovery, work-home integration supplies, unfinished tasks, time pressure) and mediation (i.e., mindfulness, work-related maladaptive thinking patterns) effects will be analyzed using the PROCESS macro for SPSS [91]. T2 measures of the studied mediators will be utilized in these analyses. In order to explore both; the inter-individual variability and the intra-individual patterns of change trajectories in the mechanisms and the main outcomes during interventions, growth curve analyses will be conducted using data from the weekly questionnaires.

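### The simple-effects follow-up gives T2/T3 group comparisons that ignore the T1 score; named, T1-adjusted contrasts would be more precise at no cost

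*Protocol article*

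**What the plan says.** Effect evaluation names the primary analysis in full: for psychological detachment and for burnout separately, a repeated-measures ANOVA with time (pre, post, follow-up) and group (CBT, MBSR, control) as factors. No covariate is named, so T1 enters only as one level of the outcome. The next step reads: "Significant interactions will be followed up with a simple effects" analysis, with Bonferroni correction.

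Objectives and hypotheses predicts that CBT will do better at T2 and T3 than MBSR and control, and better than its own T1 level. Measures states that "All four questionnaire batteries (pre-screening, T1, T2, T3) will include measures of burnout and psychological detachment", so a baseline value of each primary outcome is available for everyone. Participants and recruitment states that "block randomization based on gender will be used", on the ground that women have more difficulty detaching; the primary model has no gender term.

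**The concern.** The interaction test has four numerator degrees of freedom and says only that the arms do not all change alike. Which arm differs from which, and by how much, comes from the follow-up. A simple effect there has one of two forms:

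- **Groups compared at T2 or T3.** The contrast uses raw means. T1 is discarded, and a chance difference between arms at T1 passes into the result in proportion to the correlation.
- **Time compared within an arm.** There is no comparator. Participants are admitted because they report difficulties, so some improvement may occur in every arm without treatment. A significant change in CBT beside a non-significant one in MBSR would not show that the two differ.

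Neither is the T1-adjusted difference between arms that the hypotheses call for. At stake are wider intervals and lower power for the trial's central comparisons, and a risk that within-arm change is read as evidence of effectiveness.

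**Working it through.** **1. The plan's own sample size.** Inputs from Sample size calculation: f(V) = .25, so f² = .0625; "the probability of a Type I error to α = .05"; "the statistical power (1-β) to .95"; k = 3 groups; m = 3 times. For the multivariate group by time interaction, s = 2, df1 = (k−1)(m−1) = 4, df2 = s(N − k − (m−1) + s), noncentrality = sNf².

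- N = 151: df2 = 2(151−3−2+2) = 296, noncentrality = 2 × 151 × .0625 = 18.875, power .9500.
- N = 98: df2 = 2(98−3−2+2) = 190, noncentrality = 2 × 98 × .0625 = 12.25, power .8005.

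Both stated totals reproduce. They size the interaction test, not the pairwise contrasts.

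**2. Variance of a between-arm contrast.** Let rho be the correlation of T1 with the later score, with equal variances. Relative to raw means at one visit (1), the variance is 2(1−rho) for a difference in change and 1−rho² with T1 as covariate. The documents do not give rho, so a range is assumed.

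| rho | Raw | Change | T1-adjusted | Adjusted n per arm matching 50 raw |
|---|---|---|---|---|
| .3 | 1 | 1.40 | 0.91 | 45.5 |
| .5 | 1 | 1.00 | 0.75 | 37.5 |
| .6 | 1 | 0.80 | 0.64 | 32 |
| .7 | 1 | 0.60 | 0.51 | 25.5 |

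The last column is 50(1−rho²). Adjustment has a smaller variance than either alternative in every row.

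**3. Power.** The documents give no pairwise effect, so d = 0.5 SD is assumed. Two-sided alpha = .05/3, no requirement of a significant interaction on either side, n = 50 or 33 per arm as in Sample size calculation. Noncentrality = d/√(2v/n), where v is the relative variance; df = 3n−3, or 3n−4 with the covariate. For example, at n = 50: raw 0.5/√(2/50) = 2.50; adjusted with rho .6, 0.5/√(1.28/50) = 3.125.

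| | Raw | rho .3 | rho .5 | rho .6 | rho .7 |
|---|---|---|---|---|---|
| 50 per arm | 53% | 58% | 68% | 76% | 86% |
| 33 per arm | 35% | 38% | 47% | 54% | 66% |

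A simulation of 4,000 trials per setting agrees: at 50 per arm, raw 51%, adjusted 66% (rho .5) and 85% (rho .7).

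**4. Chance imbalance at T1.** The standard error of a T1 difference between two arms is √(2/n): 0.20 SD at 50 per arm and 0.25 SD at 33. With rho .5, a T1 difference of one standard error moves the raw T2 difference by about 0.10 or 0.12 SD.

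**5. Gender after T1.** With an assumed gender difference of 0.3 SD at both visits and 50 per arm, the simulated standard error is 0.172 at rho .5 and 0.141 at rho .7, whether or not gender is added to a model that already holds T1.

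**The case against.** A repeated-measures ANOVA with corrected simple effects is conventional and valid. Under randomisation the raw T2 and T3 contrasts are unbiased, and the interaction test uses T1 because it compares change. All of this stands: the point is about efficiency and interpretation in the follow-up step, not about a wrong test.

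The size also rests on an unknown correlation. Eligibility requires at least moderate difficulty on both primary outcomes, which may narrow the range of T1 scores and lower rho, and T1 may correlate less with T3 than with T2. At rho .3 the gain is only about 5 points of power at 50 per arm.

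Four stronger readings are tempting, and the documents do not support them:

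- **The trial as a whole wastes precision.** The interaction test does use T1, and the totals of 151 and 98 are right for the test they name.
- **Leaving out gender and recruitment round makes the standard errors materially too large.** The documents give no variance explained by either. After T1, gender adds almost nothing in the check above. Adjustment for a blocking factor or for round is also commonly left to the statistical analysis plan, so silence on it in an article is not a defect in itself.
- **The pre-screening score would bring a large further gain.** Participants are selected on it, so its correlation with later scores cannot be assumed equal to that of T1.
- **The gain in power comes partly from no longer requiring a significant interaction.** It would if only one side carried that requirement; the figures above impose it on neither.

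A statistical analysis plan may define the contrasts differently. The article, however, positively names simple effects, so this is a stated choice and not an omission.

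**Conclusion.** The point holds for the follow-up contrasts only. As written, the plan's only route to the hypothesised between-arm comparisons is a raw comparison at one visit or an uncontrolled change within one arm, although T1 is collected for everyone. Adjustment removes 9%, 25%, 36% and 49% of the contrast variance at rho .3, .5, .6 and .7. The power figures rest on d = 0.5 and three contrasts. If all three pairs are tested at both visits (six contrasts), power falls in both the raw and the adjusted analysis, but the variance ratios do not change. The structural point is certain from the text; its size is not, because rho is unknown. The change should be made, but the existing analysis is not invalid without it.

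**What to change.** - Replace the simple-effects sentence with named between-arm contrasts for each primary outcome at T2 and T3: CBT–MBSR, CBT–control and MBSR–control. Estimate them from one model per outcome for the T2 and T3 scores, with group, visit, group by visit, and the T1 score with its own slope at each visit. Report estimates with confidence intervals.
- Keep Bonferroni, over the number of contrasts actually tested.
- Include gender because randomisation is blocked on it, without claiming a material gain in precision beyond T1. Recruitment round and the pre-screening score are optional.
- Keep the T3 contrasts with control, since they are hypothesised, but interpret them with caution: Study design gives waitlist participants access to the materials after the intervention, so these contrasts need not be against an untreated group.
- Report change from T1 within arms as descriptive support, not as evidence of effectiveness.

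Cost: wording of the analysis plan only. T1 and gender are already collected.

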**Discussion:**

We expect that the CBT-based intervention will lead to greater improvements in psychological detachment from work and burnout compared to the MBSR and the waitlist control group. Additionally, we expect that the CBT-based intervention will also lead to greater enhancement of both general and work-related well-being.

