### Objectives and hypotheses

In order to advance CBT- and mindfulness-based intervention research for employees, the objectives of the present randomized control trial are: a) to evaluate the effectiveness of a MBSR intervention on psychological detachment and well-being indicators; b) to evaluate the effectiveness of a CBT-based intervention on psychological detachment and well-being indicators; c) to compare the strength of the effects of both protocols; d) to determine which mechanisms are responsible for the intervention effects (i.e., mediators) and test whether these mechanisms are general or intervention-specific; e) to explore boundary conditions (i.e., moderators) which attenuate or accentuate intervention effects. To determine the decisive ingredient in CBT-based and mindfulness interventions, the CBT protocol will predominantly be aimed at identifying and changing maladaptive thinking patterns and associated behaviors. The MBSR protocol, on the other hand, will predominantly include exercises that focus explicitly on increasing present moment awareness by using established exercises that aim to improve mindfulness practices [14, 38]. Although research has found that both CBT and MBSR protocols are effective with respect to employee well-being [14, 17, 18, 24], we tentatively assume that the CBT protocol will be superior for most of the studied outcomes as it is theory-driven, well-researched, and empirically supported for a wide range of conditions including moderate to severe symptoms of several psychological disorders [39]. It may also be more appropriate for targeting an important underlying factor contributing to poor detachment and burnout (i.e., maladaptive thinking patterns) [40]. Moreover, interventions that include some form of CBT exercises along with other exercises are found to be most effective [17, 18, 22, 41]. More precisely, we hypothesize that the CBT-based intervention will lead to higher levels of psychological detachment from work directly after the intervention (T2) and at follow-up (T3) compared to levels prior to the intervention (T1) and to MBSR and control groups. Additionally, we assume that the CBT-based intervention will lead to enhanced (general and work-specific) well-being directly after the intervention (T2) and at follow-up (T3) compared to levels prior to the intervention (T1) and to MBSR and control groups. In line with previous studies (e.g., [41]), a wider range of general (life satisfaction, depression, anxiety, stress, positive and negative affect, sleep quality) and work-related well-being (work engagement, workaholism, work-family conflict) outcomes will be assessed. Along with psychological detachment from work, burnout also represents a primary outcome as both interventions will be adapted to the work context and conditions of high job demands.

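### The planned follow-up to a significant interaction contains no between-arm contrast that uses T1, which costs precision in the comparisons that decide which programme is better

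*Protocol article*

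**What the plan says.** Under Effect evaluation, psychological detachment and burnout are each analysed by a two-way repeated measures ANOVA with time (pre, post, follow-up) and group (CBT, MBSR, control). The only follow-up named is: "Significant interactions will be followed up with a simple effects" analysis, Bonferroni-corrected. The text does not say whether this means group at each time, time within each group, or both. It does not say how many comparisons the correction covers, and it names neither a contrast of change between arms nor T1 as a covariate. The general level is given as "The significance level used in the analyses will be .05".

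The questions to be answered are comparative. One objective is "to compare the strength of the effects of both protocols" (Objectives and hypotheses). The abstract's Discussion says: "We expect that the CBT-based intervention will lead to greater improvements in psychological detachment from work and burnout", relative to MBSR and the waitlist. The detailed hypothesis in Objectives and hypotheses is worded as levels: higher detachment with CBT at T2 and T3 than at T1, and than in the other two groups.

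**The concern.** The group-by-time interaction concerns differences in change between arms, and the omnibus test uses T1 as one of its three time points. With three arms, a significant interaction does not say which arm did better, so the conclusion about CBT, MBSR and waitlist rests on the follow-up tests. Those tests either leave T1 out or do not compare arms. Finding a significant change in one arm and none in another is not a test of one arm against the other.

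What is at stake is precision. An unadjusted T2 or T3 comparison carries variance that T1 could remove, and it responds more to a chance T1 difference than an adjusted one does. It is therefore easier to obtain a significant interaction with no significant between-arm comparison to explain it.

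**Working it through.** **1. The plan's own figure.** The Sample size calculation section gives "We set the expected effect size to medium (*f(V)* = .25" for the omnibus effect, with three groups, three times, alpha .05 and power .95. For the within-between interaction in a repeated measures MANOVA (Pillai), s = 2, df1 = 4, df2 = 2(N − 3 − 2 + 2) = 2(N − 3), and noncentrality = N × 2 × 0.25².
- N = 151: df2 = 296, noncentrality 18.875, power .950.
- N = 98: df2 = 190, noncentrality 12.25, power .800.

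Both stated sizes reproduce exactly. They cover the omnibus interaction only. No between-arm comparison is powered.

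**2. Inputs for a between-arm comparison.**
- From the article: "the required total sample size is 151 participants (approximately 50 participants per group"), and the fallback of 98, about 33 per group.
- Assumed, because not stated: pairwise difference d = 0.5 SD, T1-T2 correlation r from .3 to .8, two-sided alpha .05/3 = .0167 (three pairs), and equal SDs at T1 and T2.

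**3. Formula.** Power comes from a noncentral t with 2n − 2 degrees of freedom and noncentrality d × √(n / (2v)). The variance factor v is:
- 1 for raw T2 means,
- 2(1 − r) for the difference in T1-to-T2 change,
- 1 − r² for T1-adjusted means (ANCOVA, ignoring the one degree of freedom spent on T1).

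Example, n = 50 and r = .6: noncentrality is 0.5 × √25 = 2.50 raw and 2.50 / √0.64 = 3.125 adjusted, giving power .53 and .75.

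**4. Results (d = 0.5, alpha .05/3).**

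| r | n = 50 raw | n = 50 T1-adjusted | n = 50 change score | n = 33 raw | n = 33 T1-adjusted |
|---|---|---|---|---|---|
| .3 | .53 | .58 | .38 | .34 | .38 |
| .4 | .53 | .62 | .44 | .34 | .41 |
| .5 | .53 | .67 | .53 | .34 | .46 |
| .6 | .53 | .75 | .64 | .34 | .54 |
| .7 | .53 | .85 | .78 | .34 | .65 |
| .8 | .53 | .96 | .93 | .34 | .82 |

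From unrounded values, adjustment gains about 5 to 43 points at n = 50 and 3 to 48 points at n = 33. It is at least as powerful as the other two at every r shown.

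**5. Sensitivity.**
- d = 0.35, r = .6, alpha .05/3: .25 raw against .41 adjusted at n = 50; .16 against .26 at n = 33.
- d = 0.5, n = 50, uncorrected alpha .05: the gain is 4 to 29 points over the same range of r.

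**6. Chance imbalance.** The standard error of a T1 difference between two arms of 50 is √(2/50) = 0.20 SD. A gap above 0.25 SD in either direction (z = 1.25) has probability about .21 per pair. At r = .6 it goes with an expected shift of 0.6 × 0.25 = 0.15 SD in the raw T2 difference.

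**The case against.** The strongest case for the plan is that simple effects are a conventional follow-up and suit the hypothesis as worded. It speaks of levels at T2 and T3, against T1 within the CBT arm and against the other arms, and the two families of simple effects answer those two parts. The article also never says that T1 will be ignored. This stands in part: the reading as group at each time is an inference, and the within-arm comparisons with T1 have a place. It does not remove the point, because neither family contains a between-arm contrast that uses T1, and the stated objective and the expectation of greater improvements call for one.

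Three stronger readings are tempting, and the document does not support them.
- A reader might infer a definite loss of about 20 points of power. That needs r near .6, d = 0.5, alpha .05/3 and ANCOVA as comparator, and none of the first three is stated.
- A reader might infer that the raw comparison loses power against the interaction contrast itself. Against the difference in change it loses nothing at r = .5 and has more power below that.
- A reader might infer bias. Participants are randomised, so the raw T2 or T3 difference is unbiased and its standard error already allows for chance imbalance at T1.

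Two further objections concern remedy and scope. With T1 as a covariate, T1 can no longer be a level of time, so the 3 x 3 interaction behind N = 151 would be lost if the covariate model replaced it. That is right, and it is met by keeping the ANOVA and changing only the between-arm follow-up. It may also be said that exact contrasts belong in an analysis plan that is not shown. The article, however, commits to a specific follow-up, and the point is about that choice.

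**Conclusion.** The point holds as one of precision and of fit between test and question. On either reading, the named follow-up supplies no between-arm contrast that uses T1, although T1 is measured on both primary outcomes and the trial's comparative conclusion depends on these tests. The raw between-arm comparison is valid but less precise than a T1-adjusted one. The gain from adjustment can only be given as the range in the working, since it rests on assumed values of r, d and the number of comparisons. It matters most at the fallback size, where the article says that "the total sample size of 98 participants (approximately 33 participants per group) suffice with a more standard power level of .80": that power is for the omnibus interaction, while a raw pairwise test at d = 0.5 has about one-third power. The change should be made, but the planned analysis is not invalid without it.

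**What to change.** Keep the 3 x 3 ANOVA as the omnibus test for each primary outcome, and keep any within-arm comparisons with T1. Replace the between-arm simple effects with T1-adjusted contrasts: model T2 and T3 on group with T1 as covariate, and report CBT-MBSR, CBT-waitlist and MBSR-waitlist differences at each time with 95% confidence intervals and Bonferroni-adjusted p-values. State how many comparisons the correction covers.

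The cost is one extra model per primary outcome, one degree of freedom and a short change of wording. T1 is already collected, and SPSS, which the article names, fits the model. The sample size calculation for the omnibus test is unaffected.

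### Holm's step-down rule would control the same familywise error as the planned Bonferroni correction and give somewhat more power for CBT versus MBSR

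*Protocol article*

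**What the plan says.** Under Effect evaluation, each of the two primary outcomes has its own repeated-measures ANOVA with three time points and "group as the between-subjects factor (3 levels: CBT, MBSR, control"). The level is fixed: "The significance level used in the analyses will be .05". If the interaction is significant, simple effects follow, "using the Bonferroni correction to adjust for multiple testing". The number of comparisons to be corrected for is not given.

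Objectives and hypotheses lists, among the aims, "c) to compare the strength of the effects of both protocols". The hypotheses there set CBT against MBSR and against control at T2 and at T3, and also set T2 and T3 against T1. The follow-up tests therefore include both between-arm and within-group contrasts.

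Under Sample size calculation the inputs are "the probability of a Type I error to α = .05, the statistical power (1-β) to .95", with a medium effect for the omnibus test, f(V) = .25. The result is that "the required total sample size is 151 participants (approximately 50 participants per group"). After drop-out, "the total sample size of 98 participants (approximately 33 participants per group) suffice with a more standard power level of .80". No difference or SD is given for any pair of arms.

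**The concern.** The direct comparison of the two interventions is what distinguishes this trial. If both interventions beat control, CBT versus MBSR is a smaller difference than CBT versus control, so it suffers most from a strict threshold. Bonferroni holds every comparison to the strictest threshold, even after other comparisons in the family have already been rejected. Holm relaxes the threshold after each rejection without raising the familywise limit. The power given up matters most at the fallback of about 33 per arm.

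**Working it through.** **1. The plan's own figures.** These are for the within-between interaction with k = 3 groups and m = 3 times. With s = 2: df1 = 4, df2 = s(N − k − (m − 1) + s), λ = s·N·f(V)².
- N = 151: df2 = 2(151 − 3 − 2 + 2) = 296, λ = 2 × 151 × .0625 = 18.875, power .9500.
- N = 98: df2 = 2(98 − 3 − 2 + 2) = 190, λ = 2 × 98 × .0625 = 12.25, power .8005.

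Both stated sizes reproduce. They give power for the interaction, not for any pair of arms.

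**2. Is a correction needed after the interaction test?** The plan was simulated with a 4-df interaction test at .05, then unadjusted two-sided pairwise arm comparisons at T2 and T3. Assumptions: equal SDs, correlation .5, 20,000 trials per scenario. Familywise error per outcome over the true null comparisons:

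| True state | 50 per arm | 33 per arm |
|---|---|---|
| CBT = MBSR, both .8 SD above control at T2 and T3 | .090 | .083 |
| CBT = MBSR, both .8 SD above control at T2 only | .158 | .148 |

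Unadjusted within-group time comparisons gave .14 to .26 in the non-null scenarios. One real effect opens the gate while several true nulls remain, so a correction is needed.

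**3. Holm against Bonferroni.** Take six between-arm comparisons (three pairs at T2, three at T3). The number is an assumption.
- Bonferroni tests all six at .05/6 = .0083.
- Holm orders the p-values and tests them in turn at .05/6 = .0083, .05/5 = .0100, .05/4 = .0125, .05/3 = .0167, .05/2 = .0250 and .05, stopping at the first failure.

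No Holm threshold is below .0083, so Holm rejects whatever Bonferroni rejects. Its familywise error is at most .05 for any correlation among the tests.

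**4. Power for CBT versus MBSR at T2.** Assumed gains 0/.4/.8 SD (control/MBSR/CBT) at T2 and T3, correlation .6, after the interaction test:

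| Per arm | Bonferroni over 6 | Holm over 6 | Gain |
|---|---|---|---|
| 50 | about .25 | about .33 | 8 points |
| 33 | about .14 | about .19 | 5 points |

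Simulated familywise error of Holm over T2 and T3 peaks near 4%; for Bonferroni over six it peaks near 3%. With smaller gains, for example 0/.3/.5 or 0/0/.4, Holm adds only about 1 to 2 points.

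**5. An alternative for the between-arm contrasts only.** At a single time point, if any two of the three pairwise equalities hold, so does the third. A significant 2-df test of group at that time point therefore allows pairwise tests at the same level. With .025 for each of T2 and T3, familywise error over both is at most about 4.8%. Power under gains 0/.4/.8 is about .39 (50 per arm) and .24 (33 per arm). Against Bonferroni with divisor 3 at each time point (about .34 and .20) the gain is 4 to 6 points. Under gains 0/0/.4 there is none (.249 to .242, and .123 to .116).

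**The case against.** Bonferroni is valid, prespecified and transparent, and it comes with matching simultaneous confidence intervals. Choosing a conservative valid method is a preference. The exact family is a detail that an article may leave to its analysis plan. All of this stands, and it limits the point to an efficiency gain.

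A reader might infer something stronger: with exactly three arms, a significant interaction already protects the pairs, so Bonferroni pays twice and wastes 10 to 17 points of power. The documents do not support this, for three reasons.
- The three-arm shortcut needs a 2-df test of the same three means at one time point. The plan's gate is a 4-df interaction over three time points, and step 2 shows that it leaves 8 to 16% error.
- A rise such as .34 to .50 at 50 per arm comes from testing at the full .05 at each time point, which carries about 9% error over T2 and T3.
- The claim that the pairs are tested at a third of the allowed level assumes a divisor of 3, which the protocol does not state. On that reading there is no slack in the worst case: familywise error over T2 and T3 is already .054 to .056 when both interventions beat control at T2 only.

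Replacing the Bonferroni sentence by a rule for between-arm contrasts alone would also leave the comparisons with T1 uncorrected, although the hypotheses need them.

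**Conclusion.** The point holds as a cheap improvement. Holm over the same family is never less powerful than Bonferroni and has the same familywise limit. For CBT versus MBSR at T2 the gain is about 8 points (50 per arm) or 5 points (33 per arm) under gains of 0/.4/.8 SD, correlation .6 and six comparisons. It is 1 to 2 points under smaller effects. The gains, the correlation and the divisor are assumptions, and a family enlarged by the within-group contrasts would give other figures. The comparison is like with like: Holm over six gives about the same power as Bonferroni with divisor 3 at each time point (about .33 against .34 at 50 per arm), but that divisor does not hold the error over T2 and T3 together. Nothing here makes the planned analysis invalid.

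**What to change.** In Effect evaluation, name the Holm step-down correction in place of Bonferroni. Apply it for each primary outcome over the same family of simple effects, and list that family: the between-arm contrasts and the within-group comparisons with T1.

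An optional alternative covers the between-arm contrasts only: test group (2 df) at .025 at each of T2 and T3, and, where significant, test the three pairs at that time point at .025 each. Keep a Holm correction for the within-group contrasts.

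The cost is one sentence. No new data or models are needed, because Holm works from the unadjusted p-values. The downside is that neither rule has simple matching simultaneous confidence intervals, so ordinary 95% intervals would be reported and labelled as unadjusted.
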